## Abstract

**Background:**

The specific use of methylprednisolone in severe community-acquired pneumonia (SCAP) has not yet formed a consensus. It is not clear whether the clinical efficacy of methylprednisolone in SCAP is dose-dependent, and how to balance the best efficacy with the least complications. The aim of this study is to evaluate the efficacy and safety of different doses of methylprednisolone in the adjuvant treatment for patients with SCAP.

**Methods/design:**

This is a prospective, randomized, double-blind, parallel group, placebo-controlled trial to evaluate the efficacy and safety of different doses of methylprednisolone in the adjuvant treatment for patients with SCAP. Patients with diagnosed SCAP are randomized to the following four groups at a 1:1:1:1 ratio: group 1 (control group)—standard ICU patient care+100ml of normal saline once a day for 5 days; group 2—standard ICU patient care+40mg of methylprednisolone (dissolved in normal saline with a final volume of 100ml) once a day for 5 days; group 3—standard ICU patient care+80mg of methylprednisolone (dissolved in normal saline with a final volume of 100ml) once a day for 5 days; and group 4—standard ICU patient care+120mg of methylprednisolone (dissolved in normal saline with a final volume of 100ml) once a day for 5 days. The primary outcome is PaO_2_/FiO_2_ ratio at day 5 following randomization. The secondary outcomes are 28-day mortality, ventilator-free days at 28 days, mechanical ventilation duration at 28 days, endotracheal intubation rate, time for temperature recovery, duration of vasopressors use, serum CRP and interleukin-6 level at day 5 following randomization, hospital stay, frequency of nosocomial infections, gastrointestinal hemorrhage, and hyperglycemia.

**Discussion:**

The results of our study may find the optimal dose of glucocorticoid in the adjuvant treatment of SCAP and provide evidence-based proof for clinicians to treat patients with SCAP. Since coronavirus disease 2019 (COVID-19) also belongs to community-acquired pneumonia, perhaps the results of our study will help to determine the appropriate dose of methylprednisolone in COVID-19 treatment.

**Trial registration:**

Chinese Clinical Trial Registry ChiCTR2100045056. Registered on 4 April 2021.

## Background

Community-acquired pneumonia (CAP) is a common clinical inflammatory disease, which is mainly caused by pathogenic microorganism infection. In Europe and North America, the annual incidence of adult CAP is 5–11 per thousand adult population and increases gradually with age [1]. Accounting for about 10–20% of hospitalized CAP, patients with severe CAP (SCAP) often need to be admitted to intensive care unit (ICU) for fluid resuscitation, necessary mechanical ventilation and other support treatment, and the 30 day mortality rate of these patients is as high as 23–47% [2–4]. Such a high mortality is not only related to the infection of SCAP itself, but also may be associated with the excessive inflammatory reaction after infection. The latter can cause extensive damage of alveolar epithelial cells and capillary endothelial cells, leading to the decrease of pulmonary surfactant, lung compliance, and lung consolidation, and eventually lead to the occurrence of acute respiratory distress syndrome.

From the perspective of pathological mechanism, the systemic inflammatory response produced by SCAP is the consequence of self-destruction caused by over activation of body defense mechanism, rather than the direct damage caused by pathogenic microorganism infection. Therefore, the treatment should not be limited to the control of infection and supportive treatment for respiration and circulation, but should find a way to block or reduce the self-destruction caused by the excessive inflammatory reaction and prevent tissue and cell damage.

Glucocorticoid is widely used in the treatment of severe infection because of its anti-inflammatory effect. Many evidence-based studies have reported that early application of glucocorticoid can affect the development of SCAP, promote disease recovery, and may reduce the mortality [5–8]. However, there is no consensus on the specific use of glucocorticoid in SCAP (such as type, dose, course of treatment, etc.) [4, 9, 10], and different methods of application bring diverse clinical outcomes [11–19]. Mikami et al. [13] found that administration of 40 mg of prednisolone for 3 days in patients with SCAP could promote resolution of clinical symptoms and reduce the duration of intravenous antibiotic therapy. Li et al. [16] recruited patients with SCAP complicated with septic shock to receive 80 mg of methylprednisolone or placebo for 3 days. The results showed that methylprednisolone could significantly improve oxygenation index, reduce serum C-reactive protein (CRP) level, and shorten the time of temperature recovery, duration of vasopressors use, and hospital stay, without increasing the incidence of adverse events. The findings of Li et al. were similar to the reports from another trial [18] that adopted 120mg of methylprednisolone to treat with patients with SCAP for 7 days. However, Zhao et al. [19] observed that although the improved oxygenation and the decreased levels of CRP and angiotensin II were detected after a 7-day therapy with 80–160mg of methylprednisolone, the length of hospital stay and mortality did not change, and the incidence of superinfection was significantly increased.

To sum up, the adjuvant effect of methylprednisolone in SCAP tends to be clear. However, the specific use of methylprednisolone has not yet formed a consensus, which needs further clinical demonstration. It is not clear whether the clinical efficacy of methylprednisolone in SCAP is dose-dependent, and how to balance the best efficacy with the least complications. As far as we know, no such research has been carried out.

The purpose of this superiority trial is to evaluate the efficacy and safety of different doses of methylprednisolone in the adjuvant treatment for patients with SCAP.

## Materials/design

### Setting

This prospective, randomized, double-blind, parallel group (1:1:1:1 ratio), placebo-controlled trial is to be conducted in Shengli Oilfield Central Hospital Affiliated to Binzhou Medical College. The hospital is a 1870-bed teaching hospital and located in the city of Dongying, Shandong province, China, which serves a population of about 2,170,000 people. The study will be carried out in three departments, including the ICU, the emergency ICU, and the respiratory ICU.

### Participants

All patients admitted to ICUs will be screened and evaluated on the day of admission. Patients who meet the inclusion criteria and do not meet the exclusion criteria will be invited to participate in the study.

Inclusion criteria:Over 18 years of age at the time of diagnosisWritten informed consent is signed by the subject or the authorized representativePatient diagnosed with SCAP according to the guidelines for the diagnosis and treatment of community-acquired pneumonia in Chinese adults (2016 Edition), formulated by respiratory branch of Chinese Medical Association. If a patient simultaneously meets the diagnostic criteria of CAP (shown in Table 1) and one of the following major criteria or more than three minor criteria, he/she can be diagnosed as SCAP

**Table 1 Tab1:** Clinical diagnostic criteria of CAP

1. Onset of illness in the community	
2. Clinical manifestations	
• Recent cough, expectoration, or the aggravation of symptoms of original respiratory diseases, with or without purulent sputum, chest pain, dyspnea, and hemoptysis	
• Fever	
• Signs of pulmonary consolidation and/or moist rales were presented	
• Peripheral white blood cell counts > 10×10^9^ / L or < 4×10^9^ / L, with or without left shift of nucleus	
3. New patchy infiltrations, pulmonary consolidations, “ground-glass,” or interstitial changes are shown in chest imaging, with or without pleural effusion.	

Clinical diagnosis of CAP can be established after meeting items 1, 3, and any one of the item 2, and excluding pulmonary tuberculosis, pulmonary tumor, noninfectious pulmonary interstitial disease, pulmonary edema, atelectasis, pulmonary embolism, pulmonary eosinophilic infiltration, and pulmonary vasculitis

Major criteria:Invasive mechanical ventilationSeptic shock with the need for vasopressors

Minor criteria:Respiratory rate ≥30 breaths/minPaO_2_/FiO_2_ ratio≤250 mmHg (1mmHg= 0.133kPa)Multilobar infiltratesConfusion/disorientationBlood urea nitrogen level≥7.14mmol/LHypotension (systolic blood pressure< 90mmHg) requiring aggressive fluid resuscitation

Exclusion criteria:Under 18 years of age at the time of diagnosisLong-term use of glucocorticoids due to various underlying diseases (course of treatment ≥ 1 month)Known allergy to glucocorticoidsContraindicationSystemic fungal infectionSevere mental illness and history of severe mental illnessActive peptic ulcerRecent gastrointestinal anastomosisUncontrolled diabetes mellitusUncontrolled varicella, measles and tuberculosis infectionUnwilling to receive positive therapyPregnant or breastfeeding women

### Randomization

Randomization will be based on a 1:1:1:1 allocation of pre-numbered boxes containing dosing units with methylprednisolone and normal saline and will be carried out by one of the investigators who will not participate in the inclusion of patients or in the delivery of medication. The allocation sequence will be computer-generated by a statistical expert and kept in a safe at the hospital pharmacy throughout the course of the study.

### Blinding (masking)

This trial is designed as a double-blind study to avoid introducing bias in the outcome assessment. The participants, investigators, care providers, and outcome assessors will be blinded to treatment allocation. Only pharmacists or nurses in the trial who are responsible for the randomization, separation, and blinding of the investigational drug will know the unblinded information. According to the allocation sequence, the pharmacists who do not participate in the outcome assessment will determine the investigational agent that each subject must receive. The agent solution that can be directly infused will be prepared by special nurses.

Early breaking of blind, if necessary, may be requested by the principal investigator and must occur in writing. The request may be motivated by emergency medical issues and/or legal and/or regulatory requirements. The principal investigator must document in writing the reasons for breaking the blind.

### Design

Patients with diagnosed SCAP are randomized to the following four groups at a 1:1:1:1 ratio:Group 1 (control group): standard ICU patient care+100ml of normal saline once a day for 5 days. Standard ICU patient care involves ventilatory, hemodynamic, antimicrobial, nutritional, and other supports according to the guidelines for the diagnosis and treatment of community-acquired pneumonia in Chinese adults (2016 Edition). At present, there are no relevant guidelines to recommend methylprednisolone as a therapeutic drug for SCAP, which indicates that a consensus has not been reached and disputes still exist. Thus the placebo control group is still needed.Group 2: standard ICU patient care+40mg of methylprednisolone (dissolved in normal saline with a final volume of 100ml) once a day for 5 days.Group 3: standard ICU patient care+80mg of methylprednisolone (dissolved in normal saline with a final volume of 100ml) once a day for 5 days.Group 4: standard ICU patient care+120mg of methylprednisolone (dissolved in normal saline with a final volume of 100ml) once a day for 5 days.

Researchers will explain the research procedures in detail to the subject or agent to obtain the informed consent and will evaluate intervention adherence during each visit. If a scheduled visit is delayed or canceled, the research team will contact the subject immediately. No concomitant care or intervention is prohibited during the study. The trial is planned to be followed up for 28 days after randomization. The schedule of enrolment, interventions, and assessments is shown in Fig. 1.

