### Secondary outcomes

Twenty-eight-day mortality (death proportion within 28 days of randomization)Sixty-day mortality (death proportion within 60 days of randomization)Ventilator-free days at 28 days (the number of days free from mechanical ventilator support in the first 28 days following randomization)Mechanical ventilation duration at 28 days (the number of days during mechanical ventilation within 28 days of randomization).Endotracheal intubation rate (the proportion of patients requiring endotracheal intubation within 28 days of randomization)Time for temperature recovery (the number of days required for body temperature to return to normal)Duration of vasopressors use (the number of days required for continuous use of vasopressors)Serum CRP and interleukin-6 level at day 5 following randomizationHospital stayFrequency of nosocomial infections (the number of ventilator-associated pneumonia, blood stream infection or candidemia within 28 days of randomization)Gastrointestinal hemorrhage (the proportion of gastrointestinal bleeding patients requiring additional medication, blood transfusion, or surgical intervention within 28 days of randomization)Hyperglycemia (the proportion of patients with hyperglycemia requiring insulin injection within 28 days of randomization)

All adverse events and other unintended effects of trial interventions or trial conduct will be collected and documented, regardless of severity. Participants who suffer harm from these events will be compensated accordingly.

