### Sample size

On the basis of previous study [12], it is calculated by Tukey-Kramer test that 220 participants will be required (55 in each group) to detect a difference of 50mmHg in the PaO_2_/FiO_2_ ratio between groups, assuming a standard deviation (SD) of 50mmHg in the control group (80% power, *α*= 0.05). If the follow-up rate is assumed to be 90%, 244 participants with 61 in each group will be needed. Sample size calculation was performed by PASS 11 software.

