### Statistical analysis

We will show *n* (%) for categorical variables and median (interquartile range) for continuous variables with non-normal distribution or mean (SD) for those with normal distribution. Data for the primary and secondary outcome will be analyzed on intention-to-treat analysis, and missing data will be handled by multiple imputation method. If variances are equal, comparison of continuous variables will be evaluated by one-way analysis of variance, followed by the least significance difference procedure; otherwise, the Games-Howell procedure will be followed. The *χ*^2^ test followed by the Bonferroni method will be used to evaluate the comparison of categorical variables. Subgroup analysis will be used when appropriate. SPSS 18.0 software will be employed for statistical analysis. Significance level is set at 0.05.

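### Follow-up is planned to day 28, yet 60-day mortality is listed as a secondary outcome; the two statements need to be reconciled

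*Protocol article*

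**What the plan says.** Three places in the protocol article bear on the length of follow-up.

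- **Design:** "The trial is planned to be followed up for 28 days after randomization". The next sentence refers the reader to Fig. 1 for the schedule of assessments.
- **Secondary outcomes:** two mortality outcomes are listed, "Twenty-eight-day mortality (death proportion within 28 days of randomization") and "Sixty-day mortality (death proportion within 60 days of randomization").
- **Abstract, Methods/design:** the list opens "The secondary outcomes are 28-day mortality, ventilator-free days at 28 days" and continues without any 60-day outcome.

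On missing data, the Statistical analysis section says: "Data for the primary and secondary outcome will be analyzed on intention-to-treat analysis, and missing data will be handled by multiple imputation method". No section of the text describes a day-60 visit, a telephone contact or a search of death records.

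**The concern.** Both time windows start at randomization, so the conflict cannot be removed by choosing a different origin. The text commits to an outcome that runs past the follow-up it plans. This is not detail that an article may leave to an analysis plan, because an analysis plan cannot supply data that the stated follow-up does not collect.

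If sites follow the Design sentence, a patient alive at day 28 has no defined route by which a later death becomes known. Deaths that happen to be noticed, for instance in patients still in hospital, would be counted, and deaths after discharge could be missed. Noticing would then depend on length of stay, which is itself an outcome that the doses may affect, so the undercount need not be equal across the four groups.

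There is also a reporting problem. With the outcome in one list and absent from the other, a reader cannot tell whether 60-day mortality is prespecified.

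**Working it through.** **1. Windows set side by side**

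| Item | Time stated | Within 28-day follow-up? |
|---|---|---|
| PaO2/FiO2 ratio (primary) | day 5 | yes |
| CRP and interleukin-6 | day 5 | yes |
| 28-day mortality, ventilator-free days, ventilation duration, intubation, nosocomial infection, gastrointestinal hemorrhage, hyperglycemia | 28 days | yes |
| Temperature recovery, vasopressor duration, hospital stay | none stated | not determined |
| 60-day mortality | 60 days | no |

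The excess is 60 − 28 = 32 days. Of the outcomes with a stated window, 60-day mortality is the only one that exceeds follow-up. It is also the only item in the Secondary outcomes section that is missing from the abstract's list.

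**2. How many patients are involved**

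Inputs:
- Planned enrolment N = 244, or 61 per group (Sample size: "If the follow-up rate is assumed to be 90%, 244 participants with 61 in each group will be needed").
- Mortality p = 0.23 to 0.47 (Background: "the 30 day mortality rate of these patients is as high as 23–47" per cent). This is a 30-day figure from cited studies, not a planning assumption of this trial. It is used here only as a proxy for day 28.

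Expected number alive at day 28 = N × (1 − p):
- p = 0.47: 244 × 0.53 = 129.3, about 129 (61 × 0.53 = 32.3 per group)
- p = 0.23: 244 × 0.77 = 187.9, about 188 (61 × 0.77 = 47.0 per group)

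So 53% to 77% of patients would enter days 29 to 60 with vital status not covered by the stated follow-up. The sample size section assumes 90% follow-up, that is, 10% loss or about 24 of 244. That allowance is not meant for a gap of this size.

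**3. What this does to the estimate**

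Let q be the probability of dying on days 29 to 60 among those alive at day 28. Then

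60-day mortality = p + (1 − p) × q.

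Follow-up to day 28 gives p. It gives no systematic information on q.
- If survivors are carried forward as alive, q is set to 0 and 60-day mortality repeats 28-day mortality, apart from late deaths noticed by chance. Missed deaths are at most N × (1 − p) × q. Each percentage point of q is 129 × 0.01 = 1.3 to 188 × 0.01 = 1.9 deaths across the trial.
- If survivors are treated as missing and imputed, the imputation model has few or no observed late outcomes from which to learn q, so the result reflects the model's assumptions.

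The documents give no figure for q, so the number of late deaths, and any bias between groups, cannot be sized from them.

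**The case against.** The strongest reply is that Fig. 1, to which the Design section refers directly after the 28-day sentence, is not available in the text reviewed. It may include a day-60 check. This stands, and it limits the consequence: a reader might infer that 60-day mortality cannot be observed at all, or that 129 to 188 patients have no planned day-60 assessment, and the documents do not support either statement. The count is of expected day-28 survivors only. The reply does not remove the contradiction. If Fig. 1 has a day-60 check, the Design sentence conflicts with the figure as well as with the outcome list.

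Other limits also stand:
- The missing-data rule is one general sentence. It does not say that outcomes beyond planned follow-up would be imputed, so imputation is one possible consequence and not a stated plan.
- A reader might infer that hospital stays longer than 28 days would be cut off. Nothing says so. Hospital stay has no stated window, nor have temperature recovery and vasopressor duration; discharge dates are routine hospital records, and how stays are measured is detail that an article may leave to the full protocol.
- The mortality range comes from background literature, so the survivor count is only indicative.
- The primary outcome is at day 5 and the sample size is built on it. Neither is touched, and 28-day mortality lies fully within follow-up.

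**Conclusion.** The inconsistency is real and confined to one secondary outcome. The Design section and the Secondary outcomes section cannot both be right about how long patients are followed, and the abstract's silence on day 60 adds to the doubt. Following the text as written, deaths over a 32-day period would not be systematically observed. 60-day mortality would then undercount late deaths or depend on imputation for those alive at day 28: about 129 to 188 of 244 patients, if 30-day background mortality of 23–47% is an acceptable proxy for day 28.

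This should be fixed, but a rating as critical would overstate it, since the main analysis and the 28-day mortality comparison do not depend on it. The conclusion that the texts conflict rests on no numerical assumption. The statement about unobserved deaths rests on the follow-up sentence being applied literally, with Fig. 1 unseen.

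**What to change.** Choose one of two changes.

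1. **Keep the outcome.** State in the Design section that vital status is followed to day 60 after randomization, and how it is obtained (telephone contact or record check). Add the outcome to the abstract's list. The cost is one contact or record check per survivor and a short amendment. Recruitment had begun when the article was written, so patients already past day 60 may need their status established retrospectively.
2. **Drop the outcome.** Delete 60-day mortality from the Secondary outcomes section, with a dated reason recorded before unblinding. The cost is the loss of one outcome; 28-day mortality remains.

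In either case, make the abstract, Design, Secondary outcomes and Fig. 1 agree. If the outcome is kept, say how patients with unknown day-60 status will be handled, so that the general imputation sentence is not applied by default to everyone alive at day 28.

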**Fig. 1 Fig1:**
[figure not shown]
The schedule of enrolment, interventions, and assessments

### Primary outcome

PaO_2_/FiO_2_ ratio at day 5 following randomization

### Secondary outcomes

Twenty-eight-day mortality (death proportion within 28 days of randomization)Sixty-day mortality (death proportion within 60 days of randomization)Ventilator-free days at 28 days (the number of days free from mechanical ventilator support in the first 28 days following randomization)Mechanical ventilation duration at 28 days (the number of days during mechanical ventilation within 28 days of randomization).Endotracheal intubation rate (the proportion of patients requiring endotracheal intubation within 28 days of randomization)Time for temperature recovery (the number of days required for body temperature to return to normal)Duration of vasopressors use (the number of days required for continuous use of vasopressors)Serum CRP and interleukin-6 level at day 5 following randomizationHospital stayFrequency of nosocomial infections (the number of ventilator-associated pneumonia, blood stream infection or candidemia within 28 days of randomization)Gastrointestinal hemorrhage (the proportion of gastrointestinal bleeding patients requiring additional medication, blood transfusion, or surgical intervention within 28 days of randomization)Hyperglycemia (the proportion of patients with hyperglycemia requiring insulin injection within 28 days of randomization)

All adverse events and other unintended effects of trial interventions or trial conduct will be collected and documented, regardless of severity. Participants who suffer harm from these events will be compensated accordingly.

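### Ventilator-free days are defined with no rule for death, and death also shortens the duration outcomes, so harm could be hidden or appear as benefit

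*Protocol article*

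**What the plan says.** Under Secondary outcomes the protocol article writes out three counts of days:

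- Time off the ventilator: "Ventilator-free days at 28 days (the number of days free from mechanical ventilator support in the first 28 days following randomization"
- Time on the ventilator: "Mechanical ventilation duration at 28 days (the number of days during mechanical ventilation within 28 days of randomization"
- Time on vasopressors: "Duration of vasopressors use (the number of days required for continuous use of vasopressors"

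It also lists "Time for temperature recovery (the number of days required for body temperature to return to normal", and hospital stay with no definition. None of these entries mentions death. Mortality at 28 and at 60 days is listed separately.

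The Statistical analysis section applies intention-to-treat to primary and secondary outcomes and multiple imputation to missing data. For testing it says: "If variances are equal, comparison of continuous variables will be evaluated by one-way analysis of variance, followed by the least significance difference procedure". Where variances are unequal, it turns to Games-Howell instead. Both routes compare means, and the choice between them depends on variance alone. The "median (interquartile range) for continuous variables with non-normal distribution" is a rule for display; no rank-based or time-to-event method is named.

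**The concern.** A ventilator-free-days score is meant to combine survival with freedom from the ventilator. As worded here, it measures only absence of the ventilator over a fixed 28-day window, and a patient who has died is not on a ventilator. Intention-to-treat means that each randomized patient needs a value, and the wording supplies one that rises the earlier a ventilated patient dies.

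The duration outcomes run the same way. Death ends ventilation, vasopressor use and hospital stay, so an early death yields a short duration, which normally reads as a good result. Time to temperature recovery differs: for a patient who dies febrile it has no value at all.

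The trial compares four arms to judge how dose affects efficacy and complications. If a dose raised early mortality, these outcomes could fail to show the harm or could point the wrong way.

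**Working it through.** The plan has no figure of its own to reproduce here. Its only calculation is the sample size for the primary outcome, which this point does not touch.

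**Inputs from the protocol article**
- Window: 28 days (Secondary outcomes).
- Mortality: 23–47% at 30 days (Background). This is a literature range, used here only as a contrast between two arms.
- Patients: 61 per arm, 244 in total (Sample size).

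**Assumptions, not in the document**
- Deaths occur on the ventilator on day d, with d from 3 to 10.
- Survivors are ventilated for v days, with v from 8 to 12.
- All patients are ventilated from randomization, and survivors are alike in both arms.

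**Scale.** Deaths per arm would be 61 × 0.23 = 14.0 to 61 × 0.47 = 28.7; in total 244 × 0.23 = 56 to 244 × 0.47 = 115.

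**Single patients, read literally.** Death on day 5 while ventilated: 28 − 5 = 23 ventilator-free days and 5 ventilation days. Survivor ventilated 10 days: 28 − 10 = 18 and 10. Entry does not require ventilation (septic shock or minor criteria suffice), so a patient who dies without ever being ventilated scores 28, the maximum.

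**Arm means at mortality m**
- Ventilator-free days as written: m(28 − d) + (1 − m)(28 − v)
- Ventilator-free days with death = 0: (1 − m)(28 − v)
- Ventilation days as written: m·d + (1 − m)·v

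Base case, d = 5 and v = 10:

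| | 23% mortality | 47% mortality | Difference |
|---|---|---|---|
| Ventilator-free days, as written | 0.23×23 + 0.77×18 = 19.15 | 0.47×23 + 0.53×18 = 20.35 | +1.20 |
| Ventilator-free days, death = 0 | 0.77×18 = 13.86 | 0.53×18 = 9.54 | −4.32 |
| Ventilation days, as written | 0.23×5 + 0.77×10 = 8.85 | 0.47×5 + 0.53×10 = 7.65 | −1.20 |

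The arm with more deaths looks 1.20 days better on both outcomes as written.

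**Range.** The difference in ventilator-free days (47% arm minus 23% arm) is 0.24 × (v − d) as written and −0.24 × (28 − v) with death = 0:

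| | v = 8 | v = 10 | v = 12 |
|---|---|---|---|
| As written, d = 3 | +1.20 | +1.68 | +2.16 |
| As written, d = 5 | +0.72 | +1.20 | +1.68 |
| As written, d = 7 | +0.24 | +0.72 | +1.20 |
| As written, d = 10 | −0.48 | 0.00 | +0.48 |
| Death = 0, any d | −4.80 | −4.32 | −3.84 |

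The sign reverses only when d < v. At d = v the written score does not register the extra deaths at all.

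**Smaller contrast.** At 25% v 40% mortality with d = 5 and v = 10, the written score gives 19.25 v 20.0 (+0.75) and death = 0 gives 13.5 v 10.8 (−2.7).

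**Simulation.** Four arms of 61, one at 47% mortality and three at 23%. Survivors' ventilation time was gamma-distributed with mean about 10 and SD about 6 days, capped at 28; deaths were uniform over days 1 to 9; there were 4,000 runs. ANOVA on the written score was significant in 20% of runs, with the high-mortality arm ahead by 1.19 days on average. With death = 0, ANOVA was significant in 73% of runs and Kruskal-Wallis in 65%, with that arm behind by 4.32 days.

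**The case against.** **The article is silent on death; it does not say that days after death count.** A reader might infer that the plan decides to treat early deaths as good results. The text does not go that far. Values after death might be treated as missing and sent to multiple imputation, in which case the score of 23 would not arise. That is fair, and it is why the point is worded as what the definition could do. But imputing ventilator status for the dead would be a different flaw, not a remedy.

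**A journal article condenses a fuller protocol.** This has force for hospital stay, which is only a label. It has little for ventilator-free days, where a definition is written out and its literal reading gives the wrong answer.

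**The size rests on assumptions.** It does. The day of death, the survivors' ventilation time and a mortality gap between arms are not in the document. The calculation also treats all patients as ventilated. For never-ventilated patients the written difference would be 0.24 × (28 − 28) = 0, and the death = 0 difference −0.24 × 28 = −6.72. A mixed population would therefore show less reversal, but more hidden harm.

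**The outcomes are secondary.** The primary outcome is the day-5 oxygenation ratio, and mortality is listed in its own right, so a large excess of deaths would be visible elsewhere. This stands and limits the seriousness.

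**Comparing means is defensible at about 61 per arm.** Largely so. A mean difference in days is interpretable, the Games-Howell branch covers unequal variances, and in the simulation ANOVA on the zero-scored outcome had no less power than Kruskal-Wallis. The choice of test is secondary to the missing death rule.

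**Conclusion.** The definition of ventilator-free days is fixed badly, and the duration outcomes share the weakness. This should be fixed, but it does not endanger the primary analysis.

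Over the assumed range, an arm with 47% rather than 23% mortality differs by +2.16 to −0.48 ventilator-free days as written, against −3.84 to −4.80 with death scored zero. Even at the end where the sign is right, the written score shows 0.48 of 4.80 days, a tenth of the difference.

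Three stronger conclusions that a reader might draw are not supported:

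- That the deadlier arm always looks better. The reversal needs a mortality difference and deaths that precede survivors' weaning.
- That death improves every one of these outcomes. Time to temperature recovery is undefined, not improved, for a patient who dies febrile.
- That the use of means is itself the error. Mean-based tests are a weaker, separate matter; the defect is the lack of a death rule.

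**What to change.** Before unblinding:

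1. Define ventilator-free days as zero for any patient who dies by day 28, and state that values after death are not imputed.
2. Prefer a rank-based comparison for this score, with adjusted pairwise tests, because it will be skewed with a spike at zero. The reason is the shape of the distribution, not a gain in power.
3. Analyse ventilation duration, vasopressor duration, hospital stay and time to temperature recovery with death as a competing event. Survivor-only summaries may be added if labelled descriptive, since they condition on an event after randomization that dose may affect.

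Cost: sample size and treatment do not change. Scoring death as zero needs only 28-day vital status and days of ventilation, both already planned outcomes. The competing-event analyses also need the dates of death and of each event; the article does not list the case report form items, so their availability should be confirmed. Recruitment began in April 2021, so the change should be documented as a protocol modification through the data monitoring committee described under Trial supervision. The extra analysis is small.
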